### Exercise Testing

Exercise testing is conducted using the Young Men Christian Association (YMCA) bicycle ergometer protocol at baseline and after a 12-week exercise program [46,47]. The YMCA protocol uses 2 to 4 stages of continuous exercise lasting 3 minutes, during which 2 heart rate (HR)-power output data points (steady-state HR) between 110 bpm and 150 bpm are needed. The test is designed to raise the participant’s steady-state HR to between 110 bpm and 150 bpm and 70% HR reserve or 85% of the age-predicted maximum HR (HRmax) for at least 2 consecutive stages. Using the Life-Fitness Cycle Ergometer (95Ci, Franklin Park, IL), the first 3-minute workload is set between 150 kg·m·min^-1^ and 300 kg·m·min^-1^ (25-50 watts). The speed is set at 50 rpm. HR is measured within the last minute of each stage. If an HR >110 bpm is obtained in the first 3 minutes, then only one additional 3-minute stage is performed by increasing the workload to 450 kg·m·min^-1^ (75 watts). If the second-stage HR is <110 bpm, the 3-minute third or fourth stage is performed at an additional workload of 150 kg·m·min^-1^ up to 750 kg·m·min^-1^ (125 watts), in order to obtain 2 HRs between 110 bpm and 150 bpm. At the end of the test, a 3-minute recovery period (cool down) at zero resistance is administered. HR is measured during the last minute of each stage. The 2 steady-state HRs are plotted against the respective workload on the YMCA graph sheet. The line generated from the plotted points is then extrapolated to the age-predicted HRmax, and a perpendicular line is dropped to the x axis to estimate the work rate (VO_2max_) that would have been achieved if the individual had worked to maximum capacity [46-48]. At the end of exercise testing, the participants are asked to return to the Physiotherapy department within 2 days to 3 days to commence the intervention.

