### Study Outcomes

The primary outcomes include neurocognitive performance, prevalence of HAND, viral load, and CD4 count. The secondary outcomes include maximum oxygen uptake (VO_2_), QoL, activity limitation, and participation restriction. Potential confounding variables include age, sex, level of education, vaccination, history of virologic failure, level of ART adherence, exercise adherence, ART regimen, ovulation status, history of recent vaccination, and seasonality. These variables will be measured at baseline, after 12 weeks, and 3 months after the intervention. Their change will be measured over time. Aggregation parameters will include proportion, mean, or median depending on how the data are distributed.

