### Participant Timeline

The proposed timeline for the study and planned elements is shown in Figure 1. All prospective participants were identified in a pilot study. Baseline assessments were conducted from the end of January 2021 to mid-February 2021 and covered neurocognitive performance, BP, HR, respiratory rate, assessment of physical activity readiness, QoL, CD4 count, viral load, and activity limitation and social participation. Before the intervention, all participants undergo an exercise stress test. The aerobic exercise intervention starts a day after exercise testing and lasts for 12 weeks. Following the 12-week aerobic intervention, postexercise assessments are conducted.

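### The cycle-test stage rule can defeat its own requirement of two heart rates within 110-150 bpm when a participant starts at 150 kg·m/min and stage-1 heart rate exceeds 110

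*Protocol article*

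**What the plan says.** All of the test rules are in the protocol article, Exercise Testing.

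- **Requirement.** "2 heart rate (HR)-power output data points (steady-state HR) between 110 bpm and 150 bpm are needed". The target range is to be held "for at least 2 consecutive stages". The same sentence names an individual level: 70% of HR reserve or 85% of age-predicted HRmax.
- **Starting load.** It is chosen within a range ("the first 3-minute workload is set between 150 kg·m·min^-1^ and 300 kg·m·min^-1^ (25-50 watts").
- **Stage-1 HR above 110.** The instruction is the same whatever the starting load ("then only one additional 3-minute stage is performed by increasing the workload to 450 kg·m·min^-1^ (75 watts").
- **Later stages.** "If the second-stage HR is <110 bpm, the 3-minute third or fourth stage is performed at an additional workload" of 150 kg·m/min, up to 750 (125 W). The stated aim of this branch is two HRs in the window.
- **Use.** The two HRs are plotted against load, and the line is extended to age-predicted HRmax to estimate maximal work rate and VO2max.

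Study Outcomes gives the role of the result: "The secondary outcomes include maximum oxygen uptake (VO_2_), QoL, activity limitation, and participation restriction". Participant Timeline says "Before the intervention, all participants undergo an exercise stress test", and Exercise Testing repeats the test after the 12-week program.

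**The concern.** The section states what a valid test needs and then prints a restrictive instruction that can prevent it. The largest load increase, 300 kg·m/min, can fall on participants who started at the lowest load and whose HR is already above 110. Later stages rise by only 150. If the jump carries HR past 150, one in-window point remains and the wording rules out another stage.

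The failure would not show in the data. Any two points define a line, so the test still returns a VO2max value, now resting on a point outside the range that the section itself requires.

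There is a lesser gap in wording. Stage 3 is triggered only by a stage-2 HR below 110. A participant with 105 and then 125 bpm has one valid point and no stated trigger for a third stage, although the stated aim implies one.

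**Working it through.** The plan gives no figure to reproduce here. The check traces the printed rule.

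**Inputs from Exercise Testing.** Window 110-150 bpm; stage-1 load 150 to 300 kg·m/min; stage-2 load 450 if stage-1 HR (HR1) is above 110; later steps of 150; cap 750; two to four stages.

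**Assumption, not in the article.** HR rises linearly by d bpm per 150 kg·m/min, with d from 10 to 25.

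**Step 1: size of the jump.** From a start at 150: 450 − 150 = 300, or two increments. From a start at 300: 450 − 300 = 150, or one increment.

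**Step 2: a limit that needs no assumed slope.** The window is 150 − 110 = 40 bpm wide. HR1 is above 110 in this branch, so a rise of 40 or more always ends above 150. More generally, the second HR is out of range whenever the rise exceeds 150 − HR1.

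**Step 3: start at 150, HR1 from 111 to 150.** The printed rule is valid if HR1 + 2d ≤ 150. A step of 150 is valid if HR1 + d ≤ 150.

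| d | Printed rule: HR1 giving two valid points | Step of 150 |
|---|---|---|
| 10 | 111-130 | 111-140 |
| 15 | 111-120 | 111-135 |
| 20 | none | 111-130 |
| 25 | none | 111-125 |

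Example: HR1 = 120 and d = 20 give 120 and 160 under the printed rule, against 120 and 140 with a step of 150.

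**Step 4: individual limit.** The table uses 150 bpm as the only ceiling. If HRmax is taken as 220 minus age (an assumption; the article gives no formula), 85% of it is 0.85 × 175 = 148.75 bpm at age 45 and 0.85 × 155 = 131.75 at age 65. For older participants both columns are therefore narrower than shown.

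**Step 5: the lesser gap.** For a start at 300 with d = 20: 105 at 300 and 125 at 450 leave one valid point, and a third stage at 600 would give 145. With HR1 below 110 and d ≤ 20, the third HR is HR1 + 2d < 110 + 40 = 150, so one more stage stays below 150. If a 150 start is taken to 450, the third stage may overshoot: 105, 145, 165.

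**Step 6: price of closer points.** Take 115 bpm at 25 W, d = 15 and an assumed HRmax of 180, with a 5 bpm error in stage-1 HR.

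- 50 W apart: 75 + (180 − 145)/((145 − 115)/50) = 133.3 W. With stage-1 HR read as 110 or 120 it becomes 125.0 or 145.0 W, or −6% to +9%.
- 25 W apart: 50 + (180 − 130)/((130 − 115)/25) = 133.3 W. With 110 or 120 it becomes 112.5 or 175.0 W, or −16% to +31%.

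A further stage at 450 is in range when HR1 + 2d ≤ 150, the same condition as in the printed column of step 3. Stepping by 150 and then adding 450 where HR leaves room therefore keeps the 50 W spacing wherever the printed rule would have worked, as far as the 150 bpm ceiling goes.

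**The case against.** The strongest reply is that this is a condensed article citing an established test protocol, and that Exercise Intervention assigns all fitness testing to qualified physiotherapists, who would adapt. That largely answers the lesser gap. The section allows two to four stages, states that two in-window HRs are needed, and forbids nothing after 105 and 125. A reader might infer that the rule stops the test there; it does not say so. The reply does not answer the main point, because a tester would have to depart from a printed limit of one stage and from a printed load.

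Second, the failure depends on a start at 150 and on an HR slope that the article does not give. This stands as a limit on size. At d = 10 the printed rule works for HR1 of 111-130.

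Third, the larger step gives a steadier line, and smaller steps do not guarantee success either: at d = 20 they still fail for HR1 of 131-150. Both are true. The added stage at 450 meets the first where HR allows. On the second, the smaller step gives two valid HRs over a wider range of HR1 at every d examined.

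Fourth, Results reports enrollment complete, so a new rule cannot reach baseline tests already done. This also stands, and it moves the practical weight to the count and the sensitivity analysis.

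**Conclusion.** The concern holds as a minor internal conflict. For a participant started at 150 kg·m/min with stage-1 HR above 110, the printed rule fails its own requirement whenever the 300 kg·m/min jump raises HR by more than 150 − HR1, and always when the rise is 40 bpm or more. That much follows from the text alone. The HR ranges tabulated above also rest on the assumed linear slope and on a ceiling of 150 bpm. A start at 300 is unaffected by the large jump. The missing stage-3 trigger is a gap in wording beside a stated aim, not a contradiction.

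A reader might infer more, and the article does not support it:

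- **That many VO2max values are invalid.** The article gives no HR data, so no frequency can be derived.
- **That the comparison between arms is biased.** The same rule applies to both arms, and nothing in the article shows a difference or its direction.
- **That the main conclusions are at risk.** Only the secondary outcome VO2max is affected. The primary outcomes and the sample size do not depend on this test.

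**What to change.** **Rule for any test still to be done.**

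- When stage-1 HR is above 110, raise the load by 150 kg·m/min. Add a further stage at 450 if HR leaves room, so that points 50 W apart are kept where possible.
- In every branch, continue in steps of 150 until two consecutive HRs lie within 110-150 bpm, within four stages and 125 W.
- Add no load once HR exceeds 150 bpm or the section's individual limit (70% of HR reserve or 85% of age-predicted HRmax), and flag a test that ends without two valid points.
- Use the same starting load for a participant at both visits.

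**Tests already done.** Count by arm and visit those without two in-window HRs, and report a VO2max sensitivity analysis that excludes them. The main VO2max analysis keeps everyone. Results states that data analysis has not yet been executed, so both can still be added.

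**Cost.** At most one extra 3-minute stage per test. Where HR leaves no room for 450, the points lie 25 W apart and the line is noisier, by the amount shown in the working. A start at 300 already has that spacing under the printed rule. Some participants may have a baseline test under the printed rule and a later one under the new rule; where 450 is reached at both visits, the outer loads still match.

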### Exercise Intervention

Participants in the aerobic exercise group exercise on a bicycle ergometer at a low intensity of between 60% and 80% of their HRmax as recommended by the American College of Sports Medicine (ACSM) [49]. Participants train 3 times a week for 12 weeks. Initially, participants train at 60% of HRmax, and this is increased after 4 weeks to 80% HR_max_ for the remainder of the training period. Each training session consists of 20 minutes to 30 minutes of aerobic exercise in the first 4 weeks depending on the patient’s tolerance. After the first 4 weeks, training sessions are increased to 30 minutes to 45 minutes and further increased after the eighth week to 60 minutes for the remainder of the intervention. Participants are encouraged to give their best to the moderate-intensity exercise. Participants are prepared for exercise following the ACSM guidelines [46]. All fitness testing is performed by qualified physiotherapists.

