### Trial Design

This is a parallel randomized controlled trial employing a restricted assignment scheme, where participants were allocated in a 1:1 ratio. The intervention is aerobic exercise, and the comparator is a no-treatment control group. All assessors will be blinded regarding participant identification of both the experimental and control groups.

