## Methods

### Study Setting

This study is taking place at the Exercise Immunology Clinic of the Department of Physiotherapy, University of Nigeria Teaching Hospitals (UNTH) Ituku-Ozalla, Nigeria, and the University of Nigeria Enugu Campus (UNEC). A preliminary study revealed that approximately 50% of the prospective participants that visited the UNTH ART clinic were from Enugu Metropolis. The second site, UNEC, was chosen as a more centralized location for participants who resided in Enugu Metropolis and nearby environs. Participants were purposively selected to participate. To ensure consistency, the intervention team, which is comprised of 2 qualified physiotherapists and 2 trained research assistants, was trained by the principal investigator.

We identified prospective participants during a pilot study. Prospective participants, who lived in the Enugu metropolis and surrounds, were invited by text message to attend the ART clinic. Only participants able to travel to the study site with ease were invited to participate. Participants were randomly assigned to the intervention or control group. First, a sequence of random numbers was generated using Random Restricted Software 2.0. An independent person assigned the random numbers to either the intervention or control group by placing the generated numbers into A4, opaque, sealed envelopes, with only C or E written on an inconspicuous area of the envelope. Envelopes with C are control and E are exercise. The outcome assessors (the principal investigator and clinical psychologist) enrolled participants into the study, without knowing group assignments. Outcome assessors, including the principal investigator, neurologist and clinical psychologist, and data analyst, were also blinded while conducting neurological assessments. Care physicians were asked not to suggest any form of aerobic exercise to the patients throughout the study period. Trained physiotherapists conducted the treatment. Finally, the data were coded (C for control group and B for experimental group) so that the biostatistician will not know which group is experimental or control.

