### Neuropsychological Screening

The principal investigator (who is a physiotherapist working with people living with HIV and neurological conditions), a clinical psychologist, and a neurologist (who is a specialized medical doctor) conduct the neuropsychological screening, which is conducted in 3 stages. First, we conduct a brief neuromedical screening using a pilot assessment guide; then, we administer the neuropsychological instruments and, finally, assess the subjective symptoms of HAND such as difficulty remembering recent events (people, conversations, names, commitments, where things are placed), understanding conversation or reading materials, word finding, planning activities, problem solving, concentrating, thinking clearly or logically, finding his or her way about, calculating, and following direction or instruction.

We administer neuropsychological instruments chosen for their simplicity and ease of administration in any language. Only the Hopkins Verbal Learning Test-Revised (HVLT-R) and Controlled Oral Word Association Test (COWAT) require understanding of some English words. These tests were extracted from the international neurobehavioral test battery used by the HIV Neurobehavioral Research Center [1] and a recent clinical trial on HAND [50,51]. These tests are sensitive to HAND in Nigeria [52,53]. We first screen for probable dementia using the International HIV Dementia Scale (IHDS). Confirmatory neuropsychological tests are administered in the following order: first, we administer the HVLT-R immediate recall (duration 3-5 minutes). After waiting 20 minutes to 25 minutes to administer the second part of the HVLT-R, we administer the Trail Making Test (TMT)-A and -B (5-10 minutes), verbal fluency (3-8 minutes), and the Digit Span Test (5-10 minutes). We then administer the HVLT-R delay recall. We also assess neurocognitive performance in line with the 2007 modified American Academy of Neurology criteria, also known as the Frascati criteria [1,54]. We will convert the raw scale scores using a clinical rating algorithm, to sum the scores to obtain an overall score for each participant. The latter will be used for covariate analysis, if needed.

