### Oversight and Monitoring

The trial is conducted by a team of 2 qualified physiotherapists and 2 trained research assistants, while the investigator and research supervisors monitor and oversee data collection and analysis. The intervention administrator provides daily updates regarding the trial to the chief investigator who then provides weekly updates to his supervisors. Challenges encountered during the trial are resolved by the investigators through conference meetings or other feasible alternatives.

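### The claim that all assessors are blinded is not supported for VO2max, which, as the article describes the staffing, appears to be tested at 12 weeks by the treating physiotherapists

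*Protocol article*

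**What the plan says.** Trial Design makes an unqualified statement: "All assessors will be blinded regarding participant identification of both the experimental and control groups". Study Setting then gives the detail: "Outcome assessors, including the principal investigator, neurologist and clinical psychologist, and data analyst, were also blinded while conducting neurological assessments".

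The same section describes "the intervention team, which is comprised of 2 qualified physiotherapists and 2 trained research assistants" and adds: "Trained physiotherapists conducted the treatment". Oversight and Monitoring repeats the staffing: "The trial is conducted by a team of 2 qualified physiotherapists and 2 trained research assistants". On who tests fitness, Exercise Intervention says: "All fitness testing is performed by qualified physiotherapists".

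Study Outcomes lists maximum oxygen uptake as a secondary outcome. Exercise Testing places the cycle test at baseline and after the 12-week program. It allows a first workload anywhere from 25 to 50 W and takes heart rate in the last minute of each 3-minute stage. It derives the result graphically: "The 2 steady-state HRs are plotted against the respective workload on the YMCA graph sheet". The line is then extended to age-predicted maximum heart rate and the work rate is read off the horizontal axis.

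**The concern.** Physiotherapists who supervise 12 weeks of cycling know which participants trained. If they also run the 12-week test, VO2max is assessed unblinded and the blanket statement in Trial Design does not hold for it.

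The baseline test comes before training, so the exposure is at week 12. A difference between arms could then come partly from how heart rates were read or how the line was drawn. A trial report that repeated the blanket statement would misinform anyone judging risk of bias, including readers of the updated meta-analysis that Statistical Methods says will take in these findings.

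**Working it through.** **Who tests, and are they blinded?** The article gives no figure for this, so the check compares its statements.

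1. The blinded people named in Study Setting are the principal investigator, the neurologist, the clinical psychologist and the data analyst. Their blinding is described for neurological assessments. Fitness testing is not mentioned.
2. Fitness testing belongs to qualified physiotherapists, in the plural. Study Setting and Oversight and Monitoring use that term only for the two members of the intervention team.
3. The one other physiotherapist described is the principal investigator (Neuropsychological Screening), who is a blinded assessor. One person does not account for the plural.
4. No section describes a separate blinded tester or a blinded reading of the graph.

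As staffed in the article, the 12-week test therefore falls to people who know the allocation.

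**What does the procedure leave to the tester?** The starting load may be chosen within 25 to 50 W, and the heart rate has to be read. The reading time is fixed, and the stage rules largely determine the later loads. The article does not say who plots the points.

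**How sensitive is the estimate?** A line through (W1, HR1) and (W2, HR2), extended to HRmax, gives

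W = W1 + (HRmax − HR1) × (W2 − W1) / (HR2 − HR1).

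The article gives no participant values, so the following are assumed: W1 = 50 W, W2 = 75 W, HRmax = 180 bpm.

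- *Shallow line, 110 and 130 bpm.* W = 50 + 70 × 25/20 = 137.5 W. Reading 127 for 130 gives 50 + 70 × 25/17 = 152.9 W (+11.2%).
- *Steeper line, 115 and 145 bpm.* W = 50 + 65 × 25/30 = 104.2 W. Reading 142 for 145 gives 50 + 65 × 25/27 = 110.2 W (+5.8%).
- *Both readings low by 3 bpm on the steeper line, 112 and 142.* W = 50 + 68 × 25/30 = 106.7 W (+2.4%). An error in one reading matters more than a shift common to both.

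**What would a systematic shift do to the comparison?** This too is illustrative. Take 34 per arm, no true effect, and a rater shift of b SD in one arm. The two-sided 5% t test then has noncentrality b × √(34/2) on 66 degrees of freedom. For b = 0.1, 0.2, 0.3 and 0.5, the false-positive rate is about 7%, 13%, 23% and 53%. Nothing in the article indicates which b applies, or that b differs from zero.

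**The case against.** The strongest reply is that no sentence says testers and trainers are the same people. The trial runs in a teaching hospital's physiotherapy department, which could supply other physiotherapists. The list of blinded assessors is introduced as non-exhaustive, and the statements are compatible if the fitness testers were independent and blinded. This stands as a limit on certainty. A reader might infer that the blinding statement is simply false, or that the treating staff certainly did the testing. The article supports neither as fact. It does make a universal claim and then assign an outcome to staff whom it describes only as treating, so the claim needs either support or a narrower scope.

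A second reply is that rater discretion is limited, because the reading time is fixed and the stages follow rules. That also stands. What remains is the choice of starting load, the reading and the plot.

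A third is that the sensitivity figures show how error is magnified without showing bias, and that the larger figure uses a first heart rate of exactly 110 bpm and a shallow line. This is correct, and it is why a range is given. Bias between arms would need errors that lean in one direction by group, and the article gives no evidence of that.

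Finally, VO2max is a secondary outcome and appears neither in the specific objectives nor among the outcomes named in the abstract. That limits the importance of the point but does not remove it.

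**Conclusion.** The point holds as an unsupported blinding claim for one secondary outcome. The blinding described covers the neurological assessments, and the described staffing puts the 12-week VO2max test with the treating physiotherapists. This rests on a strong inference from the staffing and would fall if independent blinded testers were used.

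A 3 bpm error in the second heart rate moves the extrapolated work rate by roughly 6% to 11% under the assumed values. A reader might take these figures as an estimate of bias in the trial. They are not one, and the size and direction of any actual bias are unknown. The blinding described for the neurocognitive outcomes is untouched, and the sample size does not depend on VO2max blinding.

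**What to change.** 1. Limit the statement in Trial Design to the neurocognitive assessments, unless the 12-week fitness testers were in fact independent and blinded. If they were, say who they were. If not, report VO2max as not blinded.
2. Have the blinded data analyst compute VO2max by a fixed formula (the straight line above, with one prespecified conversion from work rate) from the recorded load and heart-rate pairs, in place of the graph-sheet line. The file should carry a coded ID and no group letter, because Study Setting labels the groups by letter.

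Both steps still appear feasible. The Results section reports enrollment complete, data curation continuing and analysis not yet run. The second step depends on the pairs having been recorded. The cost is a wording change and a little extra analysis work, with no additional staff. Recomputation removes bias from plotting and line drawing but leaves any bias in the original heart-rate readings, so that limitation must be disclosed alongside the VO2max result.
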